# LIST OF ABBREVIATIONS

ACT Artemisinin-based combination therapy

AE Adverse event

CRF Case record form

DP Dihydroartemisinin-piperaquine

FGD Focus group discussion

G6PD Glucose-6-phosphate dehydrogenase

GCP Good Clinical Practice

GIS Geographic information system

GPS Global positioning system

Hb Haemoglobin

IDI In-depth interview

MDA Mass drug administration

MORU Mahidol-Oxford Tropical Medicine Research Unit

MPAC Malaria Policy Advisory Committee

NMCP National Malaria Control Programme

PCR Polymerase Chain Reaction

PQ Primaquine

RDT Rapid diagnostic test

SAE Serious adverse event

SEA South East Asia

SMRU Shoklo Malaria Research Unit

SOP Standard Operating Procedure

TCE Targeted chemo-elimination

WHO World Health Organisation

WWARN Worldwide Antimalarial Resistance Network

# I. BACKGROUND

The spread of artemisinin resistance in *Plasmodium falciparum,* which compromises the therapeutic efficacy of artemisinin combination treatments (ACTs), is the greatest threat to current global initiatives to control and eliminate malaria and is considered the highest priority of the WHO Global Malaria Programme [1]. If not eliminated, resistant parasites could spread across Asia to Africa, as happened with resistance to other antimalarials in the past. Conventional descriptions of the epidemiology of malaria in low transmission settings suggest that malaria prevalences are low (<10%) and heterogeneous. Most or all infections are thought to be symptomatic so the focus of malaria control activities is on the identification and treatment of symptomatic individuals. We and others have shown recently that artemisinin resistant *P. falciparum* is prevalent in Western Cambodia, and that it is now also found along the Thailand-Myanmar border and Vietnam [2,3,4,5]. We have recently developed highly sensitive quantitative PCR (qPCR) methods for parasite detection using >1mL of blood which are 5,000 times more sensitive than conventional microscopy, and 100 times more sensitive than currently used PCR. We have studied villages along the Thai-Myanmar border which are typical for the region and are classified by conventional epidemiological techniques as low-transmission (5-20% malaria prevalence). Our studies suggest that the majority of the population is infected. In Pailin, Western Cambodia, in areas where the National Malaria Control Programme and WHO believe that malaria has been all but eliminated, we have also found very high rates (>80%) of sub-microscopic parasitaemia in patients with fever or history of fever who are RDT negative. Thus, there is a lot more asymptomatic malaria in low transmission settings than previously thought, suggesting that control and elimination activities need to be rethought.

This study is designed to conduct and evaluate the efficacy of pilot implementation of targeted chemo-elimination (TCE) in selected areas with the goal of eliminating malaria in these regions. TCE differs from mass drug administration (MDA); it is a strategy used to identify specific areas where mass treatment is necessary, in this case to eliminate all malaria parasites. TCE will be targeted at communities with significant levels of subclinical infection and transmission which will be identifiable in the future by comparing rates of positivity by RDT or microscopy from new population samples against our qPCR data, which shows the true falciparum prevalence. The study will assess the feasibility, safety and acceptability of TCE and its impact on the transmission of malaria and the progression of artemisinin resistance. In addition it will evaluate the contribution of low parasitaemia carriage to transmission of artemisinin resistant malaria. These pilot studies are a necessary prelude to future scale up and policy implementation.

Dihydroartemisinin-piperaquine (DP) is a highly efficacious and inexpensive ACT which is well tolerated by all age groups when used to treat uncomplicated multidrug resistant falciparum malaria in South East Asia [6,7,8,9]. Monthly DP treatments have proved highly effective and well tolerated [3]. When used as part of a MDA strategy, the addition of a gametocytocidal drug contributes towards the goal of malaria elimination by adding a strong transmission blocking activity to the regimen. Primaquine (PQ), the only currently licensed 8-aminoquinoline, is relatively safe and very effective when used at a dose of 0.25 mg base/kg, and does not require G6PD screening [10]. Thus, we propose to evaluate the potential of a TCE programme with to eliminating malaria focally in areas where artemisinin resistance in *P. falciparum* is prevalent using DP plus PQ.

# II. OBJECTIVES

The overall aim of this study is to pilot-implement TCE in known areas of artemisinin resistance to evaluate its potential in eliminating falciparum malaria and therefore artemisinin resistance. Specifically the study will focus on the following objectives:

**Primary objective:**

To assess the feasibility, safety, acceptability, efficacy and effectiveness of TCE with DP + PQ as a tool for eliminating falciparum malaria

**Secondary objectives:**

1. Assess the efficacy of TCE in eliminating the malaria parasite reservoir
2. Assess the impact of TCE on malaria transmission
3. Describe the feasibility, safety and acceptability of TCE
4. Characterize parasite carriage using highly sensitive techniques in four geographically separate sites where resistance to artemisinin has been documented.
5. Assess the contribution of sub-microscopic parasite carriage to the transmission of artemisinin resistant parasite strains

# III. PRIMARY AND SECONDARY ENDPOINTS

## Primary endpoint

The primary endpoint will be the prevalence of falciparum malaria measured by qPCR, 12 months after the first administration of TCE.

## Secondary endpoints

Secondary endpoints will be:

- Safety and acceptability of TCE evaluated by questionnaires filled out by participants or care givers
- Effect on gametocyte carriage by TCE (measured by the proportions of gametocyte carriers over the 12 month period)
- The effect of TCE on the incidence of clinical malaria in the villages over the first 12 months
- Molecular analysis of parasite genotypes, markers of resistance and parasite population genetic structure
- Acceptability of TCE in the four study villages
- Cost estimates of TCE by sampling strategy

# IV. STUDY DESIGN

## Type of study

This is a cluster randomized, controlled, not-blinded clinical trial including residents of four Lao villages. Two villages will receive the intervention (TCE) and the other two will be the controls. The control villages will help explain non-TCE related trends in malaria prevalence over the year such as seasonal effects as well as changes in detectable falciparum over the year in the absence of treatment and on the infectivity of non-clinical parasitaemia. Five or more villages will be pre-surveyed first leading to selection of four villages per site, of which two will be randomised to TCE and two to non-TCE control. The control villages will be TCE treated the following year should TCE prove successful.

## Study sites and duration

TCE will be pilot-implemented in four sites and its effects and falciparum malaria-elimination potential will be evaluated over the course of one year; there will be two TCE villages per site and two non-TCE villages which will serve as controls. The study has been implemented in two sites on the Thai-Myanmar border and Vietnam during the first year of the project . Sites in Myanmar, Laos and Bangladesh will be added in 2015.

Prior to the beginning of the pilot-implementation of TCE in the first year, all sites will be pre-surveyed for selection of the TCE and control villages: five or more candidate villages in each region will be visited prior to TCE pilot-implementation and 50 random 2 mL blood samples per village will be taken from adults to estimate the prevalence of submicroscopic infections; 4 villages will be chosen based on a dry season malaria prevalence >10% for piloting TCE implementation during the first year. All malarias will be includes independent of the Plasmodium species. In very low density infections it is often not possible to determine the species. Once chosen, the villages will be visited regularly to engage with and prepare the community. This work leading up to the main TCE implementation will be documented as it is essential to ensure that TCE coverage will be as close as 100% as possible after excluding individuals based on appropriate exclusion criteria.

## Study populations, sample size and statistical considerations

Four villages in total per site will be identified in regions where artemisinin resistance has been documented. Each village will be of about 250-1200 people each.. Villages will be selected based on quantitative reasons (prevalence parasitaemia) and qualitative reasons (expected enthusiasm of the residents resulting in an adequate coverage). Two out of the four villages in each site will be randomized to receive TCE, the remaining two will receive no treatment (control villages).

The primary objective of this study is to test the feasibility and acceptability of implementing TCE in the six study areas, as well as its safety, efficacy and effectiveness in reducing asymptomatic malaria prevalence. Hence the primary analysis will be of the percentage falls in asymptomatic malaria prevalence in the TCE villages as determined by highly sensitive RT-PCR. We hope to see 95% reductions in prevalence rates in all sites at the end of one year.

To ensure that any reductions seen are not due to changes in endemicity unrelated to the TCE, we will also conduct a formal overall analysis comparing changes in prevalence in each study area between the TCE villages and non-TCE control villages. There will be a total of at least 4 villages in each area. For 80% power to detect a 95% fall in prevalence from a 10% initial prevalence (controlled for random changes in prevalence in the control groups) there will be a minimum required participants to be recruited and followed up of at least 152 individuals in each village. Analysis will be as a cluster randomised, repeated measures RCT, using a hierarchical logistical regression model accounting for between area (country), between cluster and between individual effects.

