# V. PROCEDURES

## Procedures timeline

### 1.1 Pre-TCE activities including community engagement

Potential villages will be visited and meetings organized with the local population and their leaders to explain the objectives of the project and to understand whether participation is acceptable and feasible. Community consent will be needed to proceed further. Five or more candidate villages, each with stable population sizes of about 250-1200 in each site will be selected based on criteria such as: easy access for community engagement and located where samples can reach the laboratories in less than 24 hours before processing. Once the study villages are chosen they will be visited regularly to engage with and prepare the community. A census will be performed and houses, work areas, and relevant migration routes will be GIS mapped. The final four villages per site will be chosen for TCE implementation based on a dry season malaria prevalence > 10%. Two of the four villages will be non-TCE control villages, two TCE. The control villages will be informed that they will receive TCE in the second year if the pilot TCE proves successful. After consultations and community engagement, health posts in each village will be set up. A presurvey where 1.5ml blood samples from 50 healthy adult volunteers in up to 20 villages will be conducted to establish sub-clinical pf malaria prevalence by qPCR.

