### 1.6 Second year

In year 2 the control villages will receive TCE while the year 1 TCE villages will be observed. However this will be reviewed based on the results of the first year. A decision on the need to conduct TCE during a second year will be based on the prevalence measures at month 12 in the TCE villages. More sites in areas of known artemisinin resistance will be added in subsequent years should TCE prove successful in reducing malaria prevalence by ≥95% from baseline levels.

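### The named primary analysis is the uncontrolled before-after fall in TCE villages, although the trial is randomised and powered for the TCE-versus-control contrast

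*Protocol*

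**What the plan says.** Section IV, Type of study: "This is a cluster randomized, controlled, not-blinded clinical trial including residents of four Lao villages". The same paragraph gives the control villages the task of accounting for trends that TCE did not cause.

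Section IV, Study populations, sample size and statistical considerations, gives two analyses in this order:

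- First, "the primary analysis will be of the percentage falls in asymptomatic malaria prevalence in the TCE villages", measured by RT-PCR. The target follows: "We hope to see 95% reductions in prevalence rates in all sites at the end of one year".
- Then, to rule out unrelated changes in endemicity: "we will also conduct a formal overall analysis comparing changes in prevalence in each study area between the TCE villages and non-TCE control villages".

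The power statement (80% power, a 95% fall from 10%, at least 152 people per village) comes after the second item and is expressed net of change in the control groups. The section closes by describing the analysis as that of a cluster randomised trial with repeated measures, using a hierarchical logistic model with area, village and individual levels.

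Section III defines the primary endpoint as qPCR falciparum prevalence 12 months after the first TCE round and names no contrast.

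Section V, 1.6 Second year, contains two decisions. Whether TCE is needed in a second year "will be based on the prevalence measures at month 12 in the TCE villages". More sites will be added "should TCE prove successful in reducing malaria prevalence by ≥95% from baseline levels".

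**The concern.** Randomisation protects the comparison between arms. It does not protect a change over time within one arm. As worded, the primary result would carry everything that moved prevalence in the TCE villages over the year. The protocol itself supplies several such forces, all present in both arms:

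- Section V, 1.1 states that "health posts in each village will be set up". The TCE protocol section adds that the posts hold RDTs and ACT+PQ, are re-supplied, and give paired villages similar access.
- Follow up (1.5) provides for treatment of clinical cases in all villages.
- Villages are selected on a dry-season prevalence above 10%, estimated from 50 adults. The part of a high reading that is sampling error should disappear if the exhaustive month-0 survey is the baseline. The part that reflects a temporarily bad period may fade by month 12 without TCE.
- Month 0 and month 12 fall at the same time of year, so a regular seasonal cycle largely cancels. A difference between transmission years does not.

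The headline efficacy figure and the decision to expand to new sites are at stake. Either could credit TCE with a general decline or charge it with a bad year.

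**Working it through.** **1. The protocol's own figures.** A 95% fall from 10% leaves 0.10 × (1 − 0.95) = 0.005, or 0.5%. For 10% versus 0.5%, two-sided 5% (assumed; alpha is not stated) and 80% power, the pooled two-proportion formula gives

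n = [1.96 × √(2 × 0.0525 × 0.9475) + 0.842 × √(0.09 + 0.004975)]² / 0.095² = 86 per group,

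or 106 with continuity correction. The stated 152 per village is 152/86 = 1.77 or 152/106 = 1.43 times as large. Neither alpha nor an intracluster correlation is given, so 152 can be neither confirmed nor refuted. The present point does not depend on it. What matters is that the figure is stated for the controlled comparison.

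**2. Which analysis each element belongs to.**

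| Element | Control term? |
|---|---|
| Named primary analysis (IV) | No |
| 95% target (IV) | No |
| Site-expansion criterion (1.6) | No |
| Additional formal comparison (IV) | Yes |
| Power statement (IV) | Yes |
| Cluster-trial hierarchical model (IV) | Yes |

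The trial is sized and modelled for the analysis it ranks second.

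**3. What the before-after fall measures.** Let P0 be baseline prevalence, s the proportional fall that would occur without TCE (seen in controls), and e the reduction due to TCE relative to control. Assume the two act multiplicatively. Month-12 prevalence in TCE villages is then P0(1 − s)(1 − e), so

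apparent fall = 1 − (1 − s)(1 − e).

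The true effect that just shows as 95% is e = 1 − 0.05/(1 − s). The documents give no control trend, so s is an assumed range:

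| Control change | True effect that shows as 95% |
|---|---|
| none | 95% |
| 25% fall | 93.3% |
| 50% fall | 90% |
| 75% fall | 80% |
| 90% fall | 50% |

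Checks: 1 − 0.50 × 0.10 = 0.95, and 1 − 0.25 × 0.20 = 0.95. In the other direction, if controls rise by 50% (s = −0.5), a true 95% effect shows as 1 − 1.5 × 0.05 = 0.925, below the criterion.

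**The case against.** The strongest reply is that the controls are already in the plan. The TCE-versus-control comparison is called formal, the sample size is set for it, and the closing sentence describes the analysis as that of a cluster randomised trial without restricting this to a secondary analysis. This stands to a large extent. A reader might infer that the randomised controls are ignored, and the documents do not support that. But the closing sentence ends the paragraph on the additional comparison and does not displace an explicit statement of what the primary analysis is. On the kindest reading the protocol is ambiguous about its primary analysis, which also needs correcting.

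Three further inferences should be resisted:

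- *That section 1.6 is one uncontrolled success rule.* It holds two decisions. The second-year decision concerns the need for TCE, for which remaining prevalence in TCE villages may be a reasonable basis in an elimination programme, and the section says the plan will be reviewed on first-year results. Only the site-expansion criterion makes a claim about effect size. The 95% in section IV is expressed as a hope.
- *That the criterion rests on a bare point estimate.* Section 1.6 is silent on estimation, and an analysis plan may cover it.
- *That an observed 95% is close to a coin toss even when the truth is 95%.* That is so for any estimate compared with its own true value, controlled or not, and says nothing about the missing control term.

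One could also say that two villages per arm make a site's randomised contrast too weak to be primary. Within one site there are only C(4,2) = 6 allocations, so the smallest two-sided permutation p-value is 2/6 = 0.33. That argues for pooling over sites, as the planned overall analysis does, and not for dropping the control term.

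**Conclusion.** The point holds as a matter of the protocol's wording. The stated primary analysis has no control term, and neither has the criterion for adding sites, in a trial whose design, power statement and model are all built on the controlled comparison. The gap is one of ranking and definition, since a controlled analysis is already planned.

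The size of the bias is unknown because no control trend is given. Under the multiplicative assumption, control falls of 50% and 75% would let true effects of 90% and 80% meet a 95% criterion, and a 50% control rise would make a true 95% effect miss it at 92.5%. If controls do not change, the two analyses aim at the same quantity. The protocol gives no reason to expect that, and it set up control villages because it might not be so.

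**What to change.** - In section IV, name as primary the randomised TCE-versus-control contrast in *P. falciparum* qPCR prevalence at month 12 (the section III endpoint). Estimate it from the hierarchical logistic model already described, accounting for site and month-0 prevalence. Keep the percentage fall within TCE villages as descriptive.
- In section 1.6, state the 95% site-expansion criterion relative to control, and say how the model result is converted to that scale. The model gives odds ratios and the criterion is a reduction in prevalence: 0.5% against 10% is a prevalence ratio of 0.05 but an odds ratio of (0.005/0.995)/(0.10/0.90) = 0.045. A definition pooled over sites is safer, since 0.5% of 2 × 152 = 304 people is about 1.5 positives per site.
- Reconcile the second-year treatment decision in section 1.6 with section IV, so that it is clear which results inform it. No particular rule is proposed here.

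**Cost.** This is a protocol amendment. Section IV says that some sites have already been implemented, and section VII requires approval of substantial amendments, so the amendment should record what outcome data had been seen by then. The headline reduction may look less favourable. No new data are needed, because the surveys already cover TCE and control villages.

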### 2.2 Other surveys

Additional surveys will be conducted on all *P.falciparum* carriers (or if the species cannot be determined) at monthly intervals to assess parasite and gametocyte dynamics. These surveys will be conducted from month 2 onwards throughout the first year.

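### The primary endpoint and the primary analysis name different quantities: falciparum prevalence at month 12, and the fall in asymptomatic malaria with no species stated

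*Protocol*

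**What the plan says.** The Primary endpoint section of the protocol gives "the prevalence of falciparum malaria measured by qPCR, 12 months after the first administration of TCE". It fixes species, assay and time point and does not mention symptoms.

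The section on study populations, sample size and statistical considerations gives the primary analysis as the "percentage falls in asymptomatic malaria prevalence in the TCE villages as determined by highly sensitive RT-PCR". No species appears there, and the word asymptomatic is not defined. The same section hopes for 95% reductions at one year and powers the trial on a 95% fall from 10%, again without a species.

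Section 1.6 Second year makes the addition of further sites depend on a reduction in malaria prevalence of at least 95% from baseline, with no species named.

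On species, Study sites and duration says, in its paragraph on choosing villages, "All malarias will be includes independent of the Plasmodium species" and then "In very low density infections it is often not possible to determine the species". Section 1.1, by contrast, describes the pre-survey as measuring falciparum. Section 2.2 Other surveys groups undetermined carriers with falciparum carriers for monthly re-sampling: "Additional surveys will be conducted on all *P.falciparum* carriers (or if the species cannot be determined) at monthly intervals". The primary objective is falciparum elimination, and section 1.4 describes the post-TCE exhaustive surveys as detecting falciparum DNA and gametocytes.

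**The concern.** A trial needs one primary variable. Here the endpoint and the analysis that is meant to estimate it differ in three respects. One names the species and the other does not. One covers everyone and the other only the asymptomatic. One is a prevalence at month 12 and the other a percentage fall. This is not detail that a protocol leaves to an analysis plan, because the protocol itself states both versions.

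Two things depend on it. The first is the headline result: how far prevalence fell, and whether that meets the 95% the investigators hope for. The second is the decision in section 1.6 on adding sites. The trial is not blinded, so an open definition could be settled after the prevalence figures are known.

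**Working it through.** **1. The three statements side by side**

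| Place in the protocol | Species | Symptoms | Measure | Assay term |
|---|---|---|---|---|
| Primary endpoint | falciparum | no restriction | prevalence at 12 months | qPCR |
| Primary analysis (sample size section) | not named | asymptomatic, undefined | percentage fall, TCE villages | RT-PCR |
| Criterion for adding sites (1.6) | not named | not stated | fall of at least 95% from baseline | not stated |

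**2. The plan's own target.** A 95% fall from 10% leaves 10% × (1 − 0.95) = 0.5%. The arithmetic is sound, but the species to which the 10% refers is not given. The figure of 152 participants per village plays no part in this point.

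**3. Effect of the species definition.** Let s be the falciparum share of infections at baseline and g the fall in other species. The protocol gives neither, so both are assumptions. With a 95% falciparum fall:

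Any-species fall = s × 0.95 + (1 − s) × g

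- s = 0.5, g = 0: 0.475 + 0 = 47.5%
- s = 0.5, g = 0.5: 0.475 + 0.25 = 72.5%
- s = 0.7, g = 0: 0.665 + 0 = 66.5%
- s = 0.7, g = 0.5: 0.665 + 0.15 = 81.5%

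In each case the falciparum figure meets 95% and the any-species figure does not.

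**4. Adding infections of undetermined species.** Assume a baseline of 10% infected: 5% determined falciparum, 2% undetermined and 3% determined other. Assume also that falciparum falls 95%, that other species do not fall, and that the undetermined infections have the same mix as the determined ones, so that 5/(5 + 3) = 0.625 of them are falciparum.

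- Month 12, determined falciparum: 5% × 0.05 = 0.25%
- Month 12, undetermined: 2% × (0.625 × 0.05 + 0.375 × 1) = 0.8125%
- Month 12, other: 3%

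Falls:

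- Determined falciparum only: 1 − 0.25/5 = 95%
- Falciparum plus undetermined: 1 − 1.0625/7 = 84.8%
- Any species: 1 − 4.0625/10 = 59.4%

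**5. Range.** Four combinations of baseline falciparum and undetermined shares were tried (70% and 10%, 50% and 20%, 30% and 30%, 20% and 50%), with other species falling 0 to 50%. The falciparum-only fall stays at 95%, falciparum plus undetermined runs from 54 to 94%, and any species from 38 to 85%. If other species also fall 95%, all three definitions give 95%.

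**6. Symptoms.** The documents give no figure from which to size the effect of an asymptomatic restriction, so none is offered.

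**The case against.** The strongest reply is that falciparum is the evident target throughout: in the objectives, the endpoint, the description of the control villages and the purpose of the exhaustive surveys. On that view the sample size section is loose wording, and asymptomatic merely describes the reservoir found in community surveys. Much of this stands, and it bears on several stronger readings that a reader might infer.

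- *That the primary analysis is defined as malaria of any species.* It is not; the section is silent. The all-species sentence concerns village selection.
- *That symptomatic carriers are removed.* No rule removes them from the numerator or the denominator. The word is undefined, which is a lesser fault.
- *That two assays are specified.* RT-PCR may simply mean real-time PCR, which would be the same method. Using one term is enough.
- *That undetermined infections bias the result in favour of TCE.* This would require their share to rise after treatment, and the protocol gives no such share. How they are coded may properly be left to an analysis plan or laboratory procedure.
- *That section 2.2 obliges them to be counted as falciparum.* That section decides who is re-sampled each month, not how the outcome is classified. As step 4 shows, counting them all as falciparum can make a true 95% falciparum fall look well short of 95%.

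It is also fair that 95% is a hope in one place and an expansion criterion in another. It is not the test criterion of the formal model.

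The reply does not remove the discrepancy itself. A reader can infer falciparum, but the primary analysis and the expansion criterion do not say so, and the analysis adds a symptom condition that the endpoint lacks.

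**Conclusion.** The point holds as a mismatch between the stated primary endpoint and the stated primary analysis variable, with a matching gap in the 95% criterion of section 1.6. That rests on the wording alone. Its numerical size is conditional: with falciparum at half of infections and falling 95%, and other species falling 0 to 50%, the any-species fall is 47.5 to 72.5%. The species shares and the falls are assumptions, and if all species respond alike the choice of species makes no difference. The calculation shows that the definition can decide whether 95% is reached; it does not show that it will.

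**What to change.** Use one variable in the Primary endpoint section, the primary analysis statement and section 1.6: P. falciparum positive by qPCR at the month-12 exhaustive survey, among all surveyed residents, whether or not symptomatic. This matches the primary objective and the survey purpose in section 1.4. Compute any percentage fall on the same variable at month 0 and month 12, delete or define asymptomatic, and use one assay term throughout.

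Because the protocol accepts that species often cannot be determined at very low density, pre-state these sensitivity analyses: falciparum prevalence with undetermined-species positives counted as falciparum and not counted, and any-species prevalence.

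The cost is protocol wording and some extra tables, with no new samples. The sponsor should expect that the sensitivity results may be less favourable than the falciparum-only figure.
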